## Abstract

**Background:**

Parkinson’s disease (PD) is a chronic, neurodegenerative disorder affecting over 137,000 people in the UK and an estimated five million people worldwide. Treatment typically involves long-term dopaminergic therapy, which improves motor symptoms, but is associated with dose-limiting side effects. Developing effective complementary, non-pharmacological interventions is of considerable importance. This paper presents the protocol for a three-arm pilot study to test the implementation of computer-based cognitive training that aims to produce improvements or maintenance of motor slower and motor fatigue symptoms in people with PD. The primary objective is to assess recruitment success and usability of external data capture devices during the intervention. The secondary objectives are to obtain estimates of variance and effect size for changes in primary and secondary outcome measures to inform sample size calculations and study design for a larger scale trial.

**Methods:**

The study aims to recruit between 40 and 60 adults with early- to middle-stage PD (Hoehn and Yahr 1–3) from National Health Service (NHS) outpatients’ clinics and support groups across North Wales, UK. Participants will be randomised to receive training over five sessions in either a spatial grid navigation task, a sequential subtraction task or a spatial memory task. Patient-centred outcome measures will include motor examination scores from part 3 of the UPDRS-III and data from movement kinematic and finger tapping tasks.

**Discussion:**

The results of this study will provide information regarding the feasibility of conducting a larger randomised control trial of non-pharmacological cognitive interventions of motor symptoms in PD.

**Trial registration:**

ISRCTN, ISRCTN12565492. Registered 4 April 2018—retrospectively registered, in accordance with the WHO Trial Registration Data Set.

**Electronic supplementary material:**

The online version of this article (10.1186/s40814-018-0375-4) contains supplementary material, which is available to authorized users.

Parkinson’s disease (PD) is a chronic, neurodegenerative disorder affecting over 137,000 people in the UK and an estimated five million worldwide [1]. It largely reflects dopaminergic cell loss in the basal ganglia and consequent disruption to ganglia-thalamo-cortical motor circuits, including the supplementary motor area [2, 3]. The primary symptoms of PD are motor in nature (bradykinesia, tremor, rigidity, balance and gait disturbance), but are known to be accompanied with, and at times preceded by, cognitive impairments, including psychomotor slowing [4]. In the absence of a cure for the illness, a major challenge is to find interventions to ameliorate these debilitating motor symptoms. For most people with PD, treatment typically involves long-term dopaminergic therapy, which is associated with a range of dose-limiting complications, and considerable healthcare costs (which exceed £3.3b annually in the UK alone [5]). In this context, the prospect of developing effective complementary, non-pharmacological interventions is of considerable importance [6, 7]. Such interventions offer the prospect of better long-term clinical management of motor symptoms, improving quality of life and reduced healthcare costs.

The goal of this study is to begin to address this challenge by piloting a novel, hypothesis-driven, non-pharmacological intervention to improve motor function and diminish motor fatigue in PD. This novel approach is based on the use of hypothesis-driven cognitive task interventions to stimulate the motor system and ameliorate motor symptoms. It is important to note that this technique differs from cognitive stimulation (or so-called brain training) interventions that aim to increase resilience to cognitive—rather than motor—decline in illnesses such as dementia. Physiotherapy and occupational interventions including motor cueing used in conjunction with walking aids, gait training, regular exercise and dance can produce benefits for people with PD [8–10]. There is also a growing interest in the development of other approaches to the treatment of motor symptoms including, for example, neuro-feedback training based on real-time functional brain imaging [11–13], and other techniques based on cortical excitation induced by transcranial magnetic stimulation (TMS) [14–16]. These latter techniques, whilst showing considerable promise, are limited in a number of ways: They are unlikely to be cost-effective for large numbers of participants, and their suitability is limited to people who are able to undergo scanning (or procedures such as TMS), for whom these methods pose no health risk, and to individuals who are willing to undergo the procedure. To our knowledge, there have been no systematic attempts to investigate the potential use of targeted cognitive-behavioural interventions for the treatment of motor dysfunction. However, advances in our knowledge about the functional neuro-anatomy of the brain, and of the underlying neuropathology of PD, suggest that such an investigation is well motivated on scientific grounds, is timely and has the potential to deliver significant healthcare benefits.

This novel approach is inspired by recent neuroscience insights into the functional links between the supplementary motor area (SMA) (a key component of the motor system in the human brain) and specific cognitive processes. The background to the current project stems from an established body of work from our own, and other research groups, on the neural substrates of high-level visuospatial processing in the neurologically normal brain [17–20]. Previously, we have shown that visuospatial processing is supported by a network of regions including the posterior parietal cortex (PPL), dorso-lateral prefrontal cortex (DLPFC) and the SMA. This is most clearly shown by functional imaging studies of brain activity during the performance of visuospatial tasks like mental rotation or mental grid navigation [21].

Several studies, including work in our own lab, have shown that people with PD are impaired in visuospatial tasks like mental rotation and grid navigation [22, 23]. Furthermore, the magnitude of impairment in mental rotation is dependent on angular disparity: people with PD show slower rates of mental rotation consistent with impairment to visuospatial processes. This is consistent with what we know about the underlying neuropathology of PD. PD is linked to dopaminergic nigrostriatal cell loss and deregulation of neurotransmitter activity in the nigrostriatal pathways of the basal ganglia. This is thought to disrupt basal ganglia-thalamo-cortical motor circuits including the SMA [24].

A key theoretical question is why visuospatial tasks like mental rotation, and grid navigation, should activate regions such as the SMA—an area traditionally associated with the planning and execution of movement [17, 25]—even when the tasks are configured to require no overt motor response [21]. One hypothesis is that visuospatial tasks, and prehensile movement, draw on certain shared underlying functional processes that are supported by an overlapping cortical network including the SMA. For example, both tasks involve spatial transformation, that is, the computation of mappings between spatial locations. In the case of movement, this is required to calculate the direction and distance (i.e. vector) between the current hand location and a to-be-grasped object (e.g. when reaching for a cup). During mental rotation (or grid navigation), the same abstract computation may be used to calculate the angular distance between two features of a rotated object or the direction and distance required to map from one grid location to another. Interestingly, other evidence supporting this putative functional link between movement and visuospatial processing comes from behavioural studies showing interference between simultaneous performance of manual and mental rotation tasks [26, 27] and from studies of visuospatial processing impairments in PD [22, 23, 28]. By targeting these cognitive processes, we can, in principle, stimulate functioning of these regions and ameliorate motor performance.

We have previously examined this possibility in a local NHS-funded pilot study (BCUHB 05/WNo03/27; unpublished). Sixteen people with early-stage (H&Y 1/2) PD, tested during the ‘ON’ phase, with age-matched controls, completed a visuospatial ‘intervention’ task of mental grid navigation and a control task of sequence memory, in two separate sessions, a week apart. Immediately before and after the two tasks, we obtained precise measures of movement onset delay and velocity with a simple reaching task completed on a touch-sensitive screen. There were no significant changes in movement onset time, or velocity following either tasks, in the control group. However, the people with PD showed a reduction in motor performance in the simple reaching task (slower mean onset and velocity) following the control task, but an enhancement of motor performance following the visuospatial task (faster mean onset and velocity). This pattern was found in 12/16 (75%) participants. These data provide some evidence that the performance of cognitive tasks that involve visuospatial processing—even after a single 20-min session—can enhance resilience to motor slowing and improve motor function, reducing hypokinesia and bradykinesia. As a form of hypothesis-driven cognitive intervention for motor dysfunction, this approach could potentially have significant clinical benefits for people with PD. If effective, the approach could form the basis of a low-cost, non-pharmacological, treatment that could be made accessible to large numbers of people in the form of a portable software/web-based programme of exercises for home use.

Before the intervention can be considered for a large-scale clinical trial, we first need to better understand the size and robustness of effects in larger samples and assess its clinical significance—whether the intervention leads to levels of improvement in movement onset and velocity that are of benefit to people with PD and whether the benefits to motor function extend to other aspects of the illness such as reduced rigidity and increased motor fluency.

This pilot trial will examine these issues and further our understanding of the potential of this novel approach to the treatment of motor dysfunction in PD. This research will form a vital step in evaluating the clinical significance of the approach, its suitability as an intervention for people with PD and the feasibility of a future large-scale clinical trial.

## Aims

The primary aim of this pilot study is to test the implementation of a computer-based cognitive training intervention designed to impact on motor slowing and motor fatigue symptoms in people with PD. We aim to explore the impact of exposure to five sessions of a spatial grid navigation intervention task in the hope that it could improve these symptoms, relative to two other control tasks: sequential subtraction and spatial memory.

### Primary objective

Feasibility for a larger scale RCT will be determined based on the following:*Recruitment*: Successful recruitment and retention of a minimum of 30 participants for the full intervention within a 12-month funding period (currently reduced to 6 months active testing/recruitment, following IRAS application and successful research passport application). If this is not possible, we would need to re-evaluate recruitment practices and adjust the timeline of future studies to reflect the challenges faced. This may require identification of additional resource implications in terms of researcher/staff time, costings, length of the intervention and delivery methods.*Acceptability/usability*: Evaluation of the usability of the external devices used to capture movement kinematic (button box) and finger tapping data (modified touchscreen gloves). In evaluating utility of custom data capture devices, we will pay particular attention to any failures/limitations in data capture (e.g. proportional data loss, reliability/consistency of measures). Additionally, we will pay attention to any difficulties that participants may experience using the equipment following informal discussion at the close of the study that may aid in the re-design of key equipment. This will be necessarily open-ended and will not rely on formal qualitative analysis.

### Secondary objective

Estimation of variance and effect sizes to inform power calculations for larger scale RCTs for primary and secondary outcome measures:A clinically relevant change in UPDRS-III motor examination scores of at least 5 points from pre to post measurements in response to spatial grid navigation training relative to the other control tasks.Improvement in movement kinematic response times over the course of the five intervention sessions in response to spatial grid navigation training relative to the other control tasks.Improvement in motor fatigue measures over the course of the five intervention sessions in response to spatial grid navigation training relative to the other control tasks.

## Methods

### Study design

We aim to conduct a three-arm, parallel, single-blind, randomised pilot trial, comparing the effect of five sessions of training on one of three cognitive intervention tasks. An adapted CONSORT (Consolidated Standards of Reporting Trials) study flow diagram is presented in Fig. 1.

**Fig. 1 Fig1:**
[figure not shown]
Protocol study flow diagram

### Study settings

Participants will be recruited from Movement Disorders outpatients’ clinics (Betsi Cadwaladr University Health Board, North Wales) and through direct contact following an earlier press release. We anticipate that most participants will prefer to be tested in their own homes, but all participants will be offered the option of being tested at local hospitals or at the School of Psychology, Bangor University. Participants will complete the study without modification to their medication or additional therapy regimens (e.g. physiotherapy, speech and language), and the study will be conducted to ensure maximum flexibility for all participants.

### Study participants

Adults with a diagnosis of Parkinson’s disease will be recruited for this study. The first participant enrolled in the study on 16/03/2018. To date, 10 (25% of 40) participants have completed the study and a further six have recently enrolled.

### Inclusion criteria

Participants of any age or sex are eligible to take part providing they meet the following criteria:Diagnosis of Parkinson’s disease in accordance with UK Brain Bank Diagnostic Criteria [29]Hoehn and Yahr stage 1–3 [30]Ability to give informed consentMontreal Cognitive Assessment [31, 32] score > 24

### Exclusion criteria

Clinical diagnosis of dementiaHistory of other significant neurological conditionsPresence of visual hallucinationsCognitive impairment (MoCA score ≤24)Significant visual impairment affecting viewing of a computer screen

### Primary clinical outcome measures

The change in the motor examination score from the Unified Parkinson’s Disease Rating Scale - III (UPDRS - III; [33]) from Session 1 to Session 5.

### Secondary outcome measures

*Motor fatigue*: Changes in the finger tapping count, the time between taps (kinesia measures) and tap dwell time (akinesia)*Motor slowing*: Changes in the response latencies (total movement time, movement initiation time and velocity) on the movement kinematic task

#### Blinding

This study is conducted single blind, in the sense that participants will not be made aware until debriefing which of the intervention conditions was expected to affect movement kinematic and motor fatigue symptoms. Double blinding is almost impossible in a cognitive intervention of this nature where the researcher is responsible for the setup and delivery of tasks in the presence of the participant. Data analysis will not be undertaken by an independent statistician, but once data has been compiled, we intend to pass anonymised raw data to an independent researcher who will generate new random IDs for all participants and revalue the intervention conditions. Our colleague will retain the linked information for all groups and new ID numbers until data analysis is completed.

### Intervention

Participants will be randomised to receive training over five sessions on Spatial Grid Navigation, Sequential Subtraction or Spatial Memory intervention tasks. Sequential Subtraction activates SMA to a similar extent as Spatial Grid Navigation, and we might expect that the sequential processing component could generalise to produce a similar improvement in movement kinematic and motor fatigue symptoms that we observed in an earlier pilot study. The spatial memory task is visually identical to the other two tasks but does not include a visuospatial sequencing component, acting as a neutral baseline task. The time between sessions will be dependent upon the availability of participants, and we will endeavour to work around participants’ other commitments and activities, as flexibly as possible to maximise retention. The variability in the time between sessions is a potential variable of interest, as the relative intensity may moderate the effectiveness of the intervention. We anticipate that participants will prefer to be tested in their own homes, but we are able to test people in the School of Psychology or in offices at local hospitals.

### Assessment measures

Figure 2 provides a schematic overview of computer-based tasks and intervention tasks.

**Fig. 2 Fig2:**
[figure not shown]
Schematic overview of each of the computer-based tasks

### Primary objective: feasibility assessment

#### Recruitment

Recruitment refers to the total number of participants who completed five intervention sessions. To determine feasibility, we expect a minimum of 30 participants to have been recruited and completed the sessions by the close of the study period.

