### Sample size

The target sample size for this study is between 40 and 60 participants. On the basis of our previous work, we estimate an attrition rate of 20%. Participants who are unable to complete the study or withdraw for any reason will be replaced. The target sample estimate is based on a maximum sample that we can reasonably expect to obtain over a 9–12-month active recruitment period, given the population and both clinical and research resources available.

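### The 30-completer feasibility criterion has no denominator, so it does not fix a level of retention, and its 6-month window conflicts with the 9–12 months behind the 40–60 target

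*Protocol article*

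**What the plan says.** Three sections of the protocol article bear on this.

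- **Aims, Primary objective.** Feasibility of a larger trial is to be judged partly on "Successful recruitment and retention of a minimum of 30 participants for the full intervention within a 12-month funding period". A parenthesis adds that this period is "currently reduced to 6 months active testing/recruitment". If the number is not reached, the team would reconsider its recruitment practices and the timeline and resources of future studies.
- **Primary objective: feasibility assessment, Recruitment.** The term is defined: "Recruitment refers to the total number of participants who completed five intervention sessions". The threshold follows: "we expect a minimum of 30 participants to have been recruited and completed the sessions by the close of the study period".
- **Sample size.** "The target sample size for this study is between 40 and 60 participants". Attrition is put at 20%. "Participants who are unable to complete the study or withdraw for any reason will be replaced". No limit on replacement is given. The target is "based on a maximum sample that we can reasonably expect to obtain over a 9–12-month active recruitment period".

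Two other places matter for interpretation. Study participants reports 10 completers as 25% of 40. Procedure sets five sessions at roughly weekly intervals or closer.

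**The concern.** One number is asked to answer two questions: can people be recruited, and do they stay? A count of completers cannot separate them. Thirty completers may come from a modest intake that mostly stayed or from a large intake of which half left, and the criterion treats the two alike. Where withdrawals are replaced, additional enrolment makes up for attrition in the count.

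The duration is a second, separate problem. The aims give 6 months of active recruitment, the sample size section 9–12 months, and the threshold itself refers only to the end of the study period. Nothing says whether the 30 or the 40–60 was revised when the window was shortened.

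Feasibility is the primary objective, so this bears on the main conclusion. A pass could hide attrition well above plan and carry a wrong attrition figure into the larger trial. A miss could be put down to recruitment practice when accrual per month was exactly as planned.

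**Working it through.** **Inputs.** Threshold 30 completers (Primary objective; Recruitment). Target 40–60, attrition 20%, replacement, 9–12 months (Sample size). Active window 6 months (Primary objective). The article derives neither the 30 nor the 40–60 by formula, so there is no stated calculation to reproduce.

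**Consistency of 30 with the target over the full window.** 40 × 0.80 = 32 and 60 × 0.80 = 48 completers. Conversely, 30 / 0.80 = 37.5, so 38 enrolled. Thirty is compatible with the lower end of the target if the full 9–12 months is available.

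**Retention implied by exactly 30 completers.** Retention = 30 / number enrolled.

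| Enrolled | Retention | Exact 95% CI |
|---|---|---|
| 38 | 79% | 63–90% |
| 40 | 75% | 59–87% |
| 50 | 60% | 45–74% |
| 60 | 50% | 37–63% |
| 75 | 40% | 29–52% |

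The last row applies if 60 means completers after replacement: 60 / 0.80 = 75 enrolled.

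**Same retention, opposite result.** Suppose true retention is 60%, that is, 40% attrition or twice the planned figure (an assumed value for illustration). The binomial probability of at least 30 completers is 0.035 with 40 enrolled and 0.96 with 60 enrolled. Both numbers lie within the stated target.

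**Completers expected in 6 months at the planned rates.** Rate = target / months; enrolled = 6 × rate. Column A takes 40–60 as randomised, so completers = 0.80 × enrolled. Column B takes 40–60 as completers, so no attrition is deducted.

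| Planned rate | Per month | In 6 months | A: completers | B: completers |
|---|---|---|---|---|
| 40 in 12 months | 3.33 | 20 | 16 | 20 |
| 40 in 9 months | 4.44 | 26.7 | 21.3 | 26.7 |
| 60 in 12 months | 5.00 | 30 | 24 | 30 |
| 60 in 9 months | 6.67 | 40 | 32 | 40 |

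Under A the expected number falls short of 30 in three of the four cases; the rate needed is 37.5 / 6 = 6.25 randomised per month. Under B it falls short in two, and 60 in 12 months just meets it; the rate needed is 30 / 6 = 5 completers per month.

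**Time to finish.** If the last enrolee needs about 4 weeks for five sessions (an assumption from the weekly schedule), enrolment effectively has 6 − 4/4.345 = 5.08 months. Reading A then gives 13.5 to 27.1 completers, below 30 in all four cases.

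**The case against.** Much of the case on the other side stands.

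- **The two problems need different windows.** A reader might infer that the same study could both pass with poor retention and fail on planned accrual. On the plan's own rates it would not. In 6 months 20–40 people are enrolled, and at 40 the count does screen out poor retention (probability 0.035 at 60% true retention). The 0.96 needs 60 enrolled, hence the longer window, over which the planned rates give 32–48 completers and a pass is expected.
- **Replacement is not the root cause.** It is tempting to say that the rule passes at 50% because withdrawals are replaced. But 30/60 is 50% with or without replacement; the missing denominator is the cause. Enrolment is also bounded by time and by a target described as the most that can be expected. Replacement adds to the problem because no cap is stated.
- **The 16–32 range depends on a reading.** Counting 10 completers as 25% of 40 suggests that the target may mean completers. The range is then 20–40, with 30 at its midpoint.
- **It is not a go/no-go rule.** A reader might take a miss as a stop. The article says that it would lead to re-evaluation, and usability is a separate feasibility element.
- **The 6 months is not plainly the criterion's window.** It stands in a parenthesis beside a 12-month funding period.
- **Reporting to CONSORT should show losses.** That makes attrition visible in the results, but the criterion still does not use it.

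None of this removes the missing denominator or reconciles the two durations. Nor is this a matter of an article leaving detail to a fuller protocol: the definition, threshold, replacement rule and both durations are all stated.

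**Conclusion.** The point holds in a limited form. The criterion is described as covering recruitment and retention, but it fixes no level of retention: across the stated target, 30 completers means anything from 75% to 50%, against an expected 80%, and as little as 40% if 60 means completers after replacement. Separately, the 6-month and 9–12-month active periods are not reconciled. At the planned rates, 6 months gives 16–32 completers or 20–40, depending on what 40–60 counts, so the criterion may be missed at the planned rate only because the window is shorter. A miss is not certain: the fastest planned rate reaches 30 on either reading if the weeks needed to finish five sessions are ignored.

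These figures assume constant accrual and, under the first reading, the plan's 20% attrition. The documents do not support the stronger conclusions that both failures would occur together, that the count can never fail on retention, or that a miss ends the programme.

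**What to change.** Keep the 30-completer count, and make three changes.

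1. State one active recruitment window throughout, and restate both the 40–60 target and the 30 for that window. Say whether 40–60 counts people randomised or completers.
2. Report accrual on its own, as participants randomised per active month.
3. Report retention on its own, as completers of five sessions divided by everyone randomised, with a 95% CI. Participants who were replaced stay in the denominator. Compare the result with the 80% implied by the plan's 20% attrition estimate, as a planning benchmark and not as a new pass mark.

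The data needed are already collected. The cost is a minor amendment during enrolment (10 participants had completed and six more had enrolled when the article was written), and reported feasibility may look less favourable.
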